## Abstract

**Background:**

Surgical hepatic resection remains the treatment of choice for patients with liver metastases from colorectal cancer despite the use of alternative therapeutic strategies. Although this procedure provides long-term survival in a significant number of patients, 50–75% of the patients develop intra- and/or extrahepatic recurrence. One possible reason for tumor recurrence may be intraoperative hematogenous tumor cell dissemination due to mechanical manipulation of the tumor during hepatic resection. Surgical technique may have an influence on hematogenous tumor cell spread. We hypothesize that hematogenous tumor cell dissemination may be reduced by using the anterior approach technique compared to conventional liver resection.

**Methods/Design:**

This is a multi-centre prospective randomized controlled, superiority trial to compare two liver resection techniques of liver metastases from colorectal cancer. 150 patients will be included and randomized intraoperatively after surgical exploration just prior to resection. The primary objective is to compare the anterior approach with the conventional liver resection technique with regard to intraoperative haematogenous tumor cell dissemination. As secondary objectives we examine five year survival rates (OS and DFS), blood loss, duration of operation, requirement of blood transfusions, morbidity rate, prognostic relevance of tumor cell detection in blood and bone marrow and the comparison of tumor cell detection by different detection methods.

**Conclusion:**

This trial will answer the question whether there is an advantage for the anterior approach technique compared to the conventional resection group with regard to tumor cell dissemination. It will also add further information about prognostic differences, safety, advantages and disadvantages of each technique.

**Trial registration:**

Current controlled trials – **ISRCTN45066244**

## Background

Despite the use of alternative therapy strategies surgical resection of colorectal liver metastases remains the treatment of choice and is associated with long-term survival in a significant number of patients [1,2]. After curative resection of colorectal liver metastases the 5-year survival rate ranges from 20% to 51% depending on preoperative selection criteria and published series [3]. However, up to 75% of resected patients will develop extra- or intrahepatic tumor recurrence [4]. One possible cause for this tumor recurrence may be intraoperative hematogenous tumor cell dissemination due to mechanical manipulation of the tumor during hepatic resection [5].

Recently, RT-PCR based protocols were developed for the detection of disseminated tumor cells [6]. We developed a sensitive and specific CK 20 RT-PCR system for detection of disseminated colorectal cancer cells in blood, bone marrow and lymph nodes [7-9]. By using the CK 20 RT-PCR, we demonstrated that there is a significantly enhanced intraoperative hematogenous tumor cell spread during resection of primary tumor and liver metastases from colorectal cancer [10,11]. In 12 of 38 patients (31,6%) with colorectal liver metastases tumor cells were detected only during or during and after surgery, possibly indicating an intraoperative tumor cell dissemination [9]. Statistical analysis revealed an increased risk for intraoperative tumor cell dissemination during major liver resection for metastases compared with minor liver resections or resection of the primary tumor (Odds ratio = 3.07; p = 0.05). These observations are in accordance with the concept of intraoperative tumor cell dissemination, because a higher degree of intraoperative manipulation of the liver and tumor in more extensive resections should result in a higher incidence of tumor cell shedding. Recent follow up of the patients with resection of colorectal liver metastases has shown, that intraoperative detection of circulating tumor cells is associated with a worse prognosis [10].

Surgical technique might influence hematogenous tumor cell spread and patient's prognosis. Initially, Liu et al. showed in a retrospective study of patients with hepatocellular carcinoma a significantly improved survival rate for patients undergoing the anterior approach technique (with primary dissection of the parenchyma and without mobilization of the liver) compared to conventional liver resection [12]. This study was followed by a prospective randomized controlled study in which the use of the anterior approach technique for liver resection in large hepatocellular carcinomas was confirmed to have a significantly better overall survival compared to the use of the conventional technique[13].

The hypothesis of this study is that intraoperative hematogenous tumor cell dissemination could be reduced or prevented by using the anterior approach technique in resection of metastasis of colorectal cancer in the liver.

## Methods/design

### Aim of the study

The objective of this trial is to compare two different surgical techniques for the resection of colorectal liver metastases with regard to intraoperative hematogenous tumor cell dissemination, survival (overall and disease-free survival), blood loss, duration of resection, transfusion requirements, complications, relevance of tumor cell detection in the bone marrow and comparison of different tumor cell detection methods.

### Trial population

The anterior approach trial includes patients with the clinical diagnosis of metastatic colorectal cancer to the liver who are being planned for elective and potentially curative (R0) resection of the right liver lobe. This study includes patients over 18 years of age who are planned for right hepatectomy (removal of segments 5–8), extended right hepatectomy (removal of segments 5–8 and parts of segment 4) or right trisegmentectomy (removal of segment 4–8). Based on the preoperative imaging the surgeon has to determine that the liver metastases can be removed with both resection techniques. Patients with extrahepatic disease, liver cirrhosis and tumor positive lymph nodes in the hepatoduodenal ligament will be excluded from the trial. A detailed overview of all eligibility criteria are given in Table 1.

**Table 1 T1:** Eligibility Criteria

**Inclusion criteria** (At study enrolment)
• Patients being considered for a potentially curative (R0) right hepatectomy (removal of segments 5,6,7,8), extended right hepatectomy (removal of segments 5,6,7,8, part of segment 4) or right trisegmentectomy (removal of segments 4,5,6,7,8) for colorectal liver metastases
• Age equal or greater than 18 years
• Absence of any psychological, familial, sociological or geographical condition potentially hampering compliance with the study protocol, follow-up schedules or from signing informed consent
• Written informed consent from each patient or the patient's legal guardian prior to entering the study
• No evidence of active or former concurrent malignant diseases (except non-melanous skin cancer)

**Exclusion criteria**

• Any extrahepatic disease, even if this will be resected concomitantly
• Liver cirrhosis
• Grossly positive lymph nodes in the hepatoduodenal ligament
• Positive margins after liver resection (R1) (Patients will be excluded from further follow up, the patient's data however will be recorded).
• Patients with an intraoperative blood loss of >= 2000 cc will be excluded from the analysis of tumor cell detection in blood samples but will be included in the rest of the analyses.

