### Sample size and statistical consideration

150 patients will be accrued to this study. Patients who underwent R1 resection and patients with an intraoperative blood loss of greater than 2000 cc will be excluded.

The sample size of this trial was calculated with regard to the previous results and data from our study on hematogenous tumor cell dissemination during resection of liver metastasis from colorectal cancer [10] and the study on the use of the anterior approach as a new liver resection technique in patients with hepatocellular carcinoma [12]. For statistical sample size calculation a 1:1 randomization in both treatment groups was assumed.

From the analysis of the previous data we expect to detect a difference of at least 30% in the proportion of intraoperative tumor cell dissemination between the two groups. The incidence of hematogenous tumor cell dissemination in the conventional group is reported to be 50–55% and it will be expected to be 15–20% in the anterior resection groups. To achieve a power of 90% (beta = 0.1) approximately 112 patients have to be recruited (two-sided test, Type I error of 5%). Due to the expectation that about 25% of all the patients will have circulating tumor cells at baseline we have to increase the total number of randomized patients to 150 patients (75 in each arm). With this sample size the study will have adequate power to address the primary objective.

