### Randomisation, stratification and blinding

The study is conducted in a prospective randomized manner. After giving informed consent and inclusion into the study, patients will be randomized in the operating room after surgical exploration just prior to resection by using sealed opaque serial numbered envelopes. These envelopes will be supplied by the Clinical Trials Centre (KSC) of the Department of Surgery, University of Heidelberg. The patients will be randomized 1:1 into each arm of the two different liver resection techniques. As stratification factors, the participating institution and the Fong score will be used [15]. The Fong score predicts the risk of recurrence after surgical resection of colorectal metastases to the liver. Two strata will be used (Fong score 0–2 and 3–5).

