### Endpoints

As primary endpoint, we choose the tumor cell detection rate in blood samples obtained intraoperatively using a CK 20 RT-PCR. The method is already established and this was the endpoint for the sample size calculation and further decision making. As secondary endpoints, overall survival and disease-free survival will be recorded during the follow-up in both groups. Further secondary endpoints are blood loss, duration time of resection, number of blood products transfused, prognostic relevance of tumor cell dissemination to the bone marrow, and postoperative complications. All these parameters will be collected prospectively as part of the study protocol.

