### Analysis

We evaluate the influence of two different liver resection techniques on the incidence of intraoperative hematogenous tumor cell dissemination in patients with colorectal liver metastases. Patients with circulating tumor cells present in the bloodstream at baseline (before operation) will be excluded from the primary analysis, hence the primary endpoint is the presence of disseminated tumor cells after liver resection. Details of the timing of the different blood samples drawn from each patient are provided.

The analyses will be performed as intention to treat analyses.

An interim analysis regarding the incidence of intraoperative tumor cell dissemination between the two arms in this study will be undertaken after the randomization of the first 75 patients. If the p-value is < 0.005, the study will be terminated and it will be concluded that the anterior approach technique significantly reduces intraoperative tumor cell dissemination. If the p-value is > 0.65 the trial will be terminated and it will be concluded that there is no significant difference between the two techniques with regard to intraoperative tumor cell dissemination. For a p-value between 0.005 and 0.65, the study will be continued to the total number of 150 patients. The interim analysis is planned using the O'Brien-Fleming boundary with a provision to stop early in favor of the null hypothesis.

Primary comparison of the proportion of patients with disseminated tumor cells in the blood after liver resection will be carried out by Fisher's exact test.

Secondary endpoints as blood loss and duration time of resection will be evaluated by t-test, and amount of used blood units and complication rates will be evaluated by Fisher's exact test. Survival probabilities will be estimated by Kaplan-Meier method and groups will be compared using the log-rank test. A comparison of survival curves will be only feasible after long term follow-up, currently estimated as at least three years. Prognostic relevance of tumor cell detection in blood and bone marrow will be assessed using proportional hazards regression.

The Cochran's Q test will be performed to correlate PCR results with timing of blood collection.

Tumor cell detection rates in blood versus bone marrow samples will be compared with the Mc Nemar's test.

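### Stopping follow-up of patients with R1 margins makes the survival comparison depend on a result of the randomised operation and contradicts intention to treat

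*Protocol article*

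**What the plan says.** Under Randomisation, stratification and blinding, the protocol article states that "patients will be randomized in the operating room after surgical exploration just prior to resection". Margins are therefore known only after allocation.

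Table 1, Exclusion criteria, nevertheless lists positive margins (R1) and rules: "Patients will be excluded from further follow up", adding only that their data are still recorded. The sample size section adds: "Patients who underwent R1 resection and patients with an intraoperative blood loss of greater than 2000 cc will be excluded". It does not say from which analysis.

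Under Endpoints: "As secondary endpoints, overall survival and disease-free survival will be recorded during the follow-up in both groups". The abstract gives the horizon for both as five years. Under Analysis: "Survival probabilities will be estimated by Kaplan-Meier method and groups will be compared using the log-rank test", and "A comparison of survival curves will be only feasible after long term follow-up, currently estimated as at least three years". The same section states that "The analyses will be performed as intention to treat analyses", and it names no exception for survival.

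**The concern.** An eligibility criterion has to be settled before randomisation. R1 status is produced by the randomised operation, and the two techniques differ in the order of mobilisation, transection and outflow control, so the R1 rate could differ between arms. Ending follow-up at R1 has three consequences:

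- It removes one plausible route, margin clearance, by which a technique could help or harm survival.
- It removes patients who plausibly have a poorer prognosis, possibly in unequal numbers, so the remaining groups are no longer the ones randomisation made comparable.
- It does so at data collection. An analysis plan can redefine an analysis set, but it cannot supply recurrence and death times that nobody recorded.

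Survival matters to how this trial will be read. The Background rests on a survival benefit of the anterior approach in hepatocellular carcinoma, and the Discussion proposes tumour cell detection as a surrogate marker. The proportional hazards analysis of tumour cell detection loses the same patients and their events.

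**Working it through.** **What the plan's figures cover.** The article gives no R1 rate and no survival power, so there is no stated figure on this point to reproduce. The sample size concerns the primary endpoint only: 112 / (1 − 0.25) = 149.3, rounded up to 150. The whole allowance goes to patients with tumour cells at baseline; nothing is set aside for R1.

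**Setting the statements side by side.**
1. Randomisation comes before resection, so margin status is a post-randomisation result.
2. R1 patients are not followed further (Table 1).
3. Overall and disease-free survival are obtained during follow-up (Endpoints) and compared between arms after at least three years (Analysis).
4. Analyses are by intention to treat (Analysis).

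Statements 2, 3 and 4 cannot all hold. Keeping the data already recorded for R1 patients does not help, because those data contain no later recurrence or death times. The next bullet of Table 1 shows that a narrower rule was possible: patients with blood loss of 2000 cc or more leave only the blood-sample tumour cell analysis and stay in the others.

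**Patients left for survival.** Expected number = 150 × (1 − r), with r an assumed overall R1 rate:

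| r | followed |
|---|---|
| 5% | 142.5 |
| 10% | 135 |
| 15% | 127.5 |
| 20% | 120 |

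**A difference that disappears.** Let r be the R1 rate in an arm, and S0 and S1 the 5-year survival after R0 and R1, assumed equal across arms. Survival among all randomised in that arm is (1 − r)·S0 + r·S1. The difference between arms is then (difference in r) × (S0 − S1), while the R0-only difference is S0 − S0 = 0 by construction. All inputs below are assumptions, with S0 = 45%.

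| R1 by arm | S1 | All randomised | Difference | R0-only |
|---|---|---|---|---|
| 20% vs 10% | 15% | 0.8×0.45 + 0.2×0.15 = 39% vs 0.9×0.45 + 0.1×0.15 = 42% | 3 points | 0 |
| 20% vs 10% | 20% | 0.8×0.45 + 0.2×0.20 = 40% vs 0.9×0.45 + 0.1×0.20 = 42.5% | 2.5 points | 0 |
| 20% vs 5% | 20% | 40% vs 0.95×0.45 + 0.05×0.20 = 43.75% | 3.75 points | 0 |
| 10% vs 10% | 20% | 42.5% vs 42.5% | 0 | 0 |

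**A difference that appears.** Suppose instead that survival among all randomised is 42% in both arms, with R1 in 20% versus 10% and S1 = 15%. The R0 patients then show (0.42 − 0.2×0.15)/0.8 = 48.75% versus (0.42 − 0.1×0.15)/0.9 = 45%. That is a spurious 3.75 points in favour of the arm with more positive margins. The bias can run either way.

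**Events lost.** With R1 in 15% of both arms, S0 = 45% and S1 = 15%, the share of 5-year deaths that goes unobserved is 0.15×0.85 / (0.15×0.85 + 0.85×0.55) = 0.1275/0.595 = 21%. Because the rates are equal, this measures lost information, not bias between arms.

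**The case against.** The strongest reply is about weight. Stopping follow-up cannot touch the primary endpoint, because that blood sample is drawn immediately after resection. The survival endpoints are secondary and the trial is not sized for them. Every rate above is assumed, and nothing in the article suggests that R1 differs by arm: both arms have the same permitted resections, and the surgeon must consider both approaches possible before randomisation. With equal R1 rates the first illustration gives no bias. Even the 3-point difference would go unseen with complete follow-up. Its standard error with 75 per arm is √(0.39×0.61/75 + 0.42×0.58/75) = 0.080, so 0.03 is about 0.37 standard errors and power is roughly 7%.

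It can also be said that perioperative data on R1 patients are kept, that the sample size sentence names no analysis, that death dates may be retrievable later, and that patients with achieved R0 are a sensible population for a prognostic question. Disease-free survival after R1 does need a special convention.

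Most of this stands as a limit on size and priority. It does not remove the contradiction. Low power is no reason to accept a biased estimate, and the published curves will be read as a comparison of techniques. Intent to achieve R0 is already required at enrolment, so restricting further to achieved R0 adds only selection after randomisation. The need for a convention applies to disease-free survival and gives no ground for dropping deaths from overall survival.

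**Conclusion.** The concern holds. As written, the R1 rule conflicts with the stated intention-to-treat principle, and no other part of the article restores follow-up for these patients. The planned comparisons would estimate survival among patients with clear margins after each technique, which is a different question from the one posed.

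The size and direction of the bias cannot be determined, because the article gives neither R1 rates nor survival after R1. On assumed R1 rates of 5% to 20%, and assumed 5-year survival of 45% after R0 and 15% to 20% after R1, the distortion between arms runs from 0 with equal R1 rates to a few percentage points. Between 7.5 and 30 of the 150 patients would be lost to the survival analyses. The damage is confined to overall survival, disease-free survival and the prognostic regression, unless the sample size sentence is also meant to apply to the primary analysis, which it leaves open.

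**What to change.** 1. Delete R1 from the exclusion criteria in Table 1 and from the exclusion sentence in the sample size section. For any exclusion that remains there, name the analysis it applies to.
2. Follow R1 patients on the same schedule and forms as everyone else.
3. Analyse overall survival in all randomised patients by assigned arm. Do the same for disease-free survival, with a convention for R1 fixed in advance, for example an event at the date of surgery. The exact convention is a matter of choice; stating one is not.
4. Report the R1 rate by arm as an outcome, and keep the R0-only survival comparison as a sensitivity analysis.
5. For R1 patients already randomised and released from follow-up, resume collection of at least survival status, and recurrence where records allow.

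The cost is a protocol amendment and follow-up forms for a minority of patients. Routine follow-up takes place at least yearly, so no additional trial procedures are needed. At the time of writing 61 of 150 patients had been randomised, so the remaining 89 can be covered from the start.

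### The primary tumour-cell comparison drops patients by blood loss, a post-randomisation outcome of the technique, so the analysed subset is not protected by randomisation, contradicts intention to treat and is not uniquely defined

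*Protocol article*

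**What the plan says.** All references are to the protocol article.

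- **Endpoints.** "As primary endpoint, we choose the tumor cell detection rate in blood samples obtained intraoperatively using a CK 20 RT-PCR". Blood loss is also an endpoint: "Further secondary endpoints are blood loss, duration time of resection, number of blood products transfused". The Analysis section compares it between arms by t-test.
- **Exclusion criteria (Table 1).** "Patients with an intraoperative blood loss of >= 2000 cc will be excluded from the analysis of tumor cell detection in blood samples". The same entry keeps these patients in every other analysis. In the same list, R1 patients leave further follow-up but their data are recorded.
- **Sample size and statistical consideration.** "Patients who underwent R1 resection and patients with an intraoperative blood loss of greater than 2000 cc will be excluded". The increase from 112 to 150 patients is justified by baseline-positive patients alone.
- **Randomisation, stratification and blinding.** "patients will be randomized in the operating room after surgical exploration just prior to resection".
- **Analysis.** "The analyses will be performed as intention to treat analyses". Also: "Patients with circulating tumor cells present in the bloodstream at baseline (before operation) will be excluded from the primary analysis".
- **Clinical evaluation.** A patient whose technique is changed during surgery for safety is removed from the study.

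**The concern.** Blood loss during resection arises after allocation and may depend on the technique allocated. Using it to decide who enters the primary comparison lets one outcome of treatment select the patients in whom another is measured. If the techniques differ in how often loss reaches 2000 cc, and tumour-cell detection differs in those patients, Fisher's test on the remainder compares groups that randomisation did not form. The observed difference could then be too large or too small.

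The baseline-positive exclusion is a different matter. Under Sample acquisition, that blood is drawn after induction of anaesthesia, before randomisation, so selecting on it keeps the arms comparable.

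The plan also does not define one primary set. Two sections state the blood-loss rule differently, one of them adds R1 patients, and neither fits the intention-to-treat sentence.

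**Working it through.** **1. The plan's own figures.** Inputs from the sample size section: 50–55% detection in the conventional arm, 15–20% in the anterior arm, a 30-point difference, two-sided 5%, 90% power, 1:1 allocation, 25% baseline-positive.

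- Exact power of the two-sided Fisher test at 56 per arm, 50% vs 20%: 89.8%. The stated figure of about 112 evaluable patients reproduces.
- 112 / (1 − 0.25) = 149.3, hence 150. Conversely 150 × 0.75 = 112.5. Nothing is left over for blood-loss or R1 exclusions.

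**2. Power if the exclusion stays.** The documents do not give the share of patients reaching 2000 cc, so the losses L below are assumed. Patients per arm = 150 × 0.75 × (1 − L) / 2, with Fisher power at 50% vs 20%. Number to randomise to restore 112 = 112 / [0.75 × (1 − L)].

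| L | per arm | power | to randomise |
|---|---|---|---|
| 0% | 56 | 89.8% | 150 |
| 5% | 53 | 87.8% | 158 |
| 10% | 51 | 86.3% | 166 |
| 15% | 48 | 83.1% | 176 |
| 20% | 45 | 81.5% | 187 |

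**3. Possible bias with no true effect.** In each arm let p be the detection rate in all baseline-negative patients, e the share excluded and r the detection rate among the excluded. The analysed rate is (p − e·r) / (1 − e). Take p = 0.35 in both arms; e and r are assumptions.

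| e, arm A vs arm B | r | analysed A | analysed B | A − B, points |
|---|---|---|---|---|
| equal (10% vs 10%) | 0.80 | 0.300 | 0.300 | 0 |
| 15% vs 5% | 0.35 (unrelated to bleeding) | 0.350 | 0.350 | 0 |
| 5% vs 2% | 0.60 | 0.337 | 0.345 | −0.8 |
| 5% vs 2% | 0.80 | 0.326 | 0.341 | −1.5 |
| 15% vs 5% | 0.60 | 0.306 | 0.337 | −3.1 |
| 15% vs 5% | 0.80 | 0.271 | 0.326 | −5.6 |
| 20% vs 5% | 0.80 | 0.2375 | 0.326 | −8.9 |
| 15% vs 5% | 0.20 (dilution) | 0.376 | 0.358 | +1.9 |

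Worked row, 15% vs 5% at r = 0.80: (0.35 − 0.12) / 0.85 = 0.271 and (0.35 − 0.04) / 0.95 = 0.326. Starting from 56.25 baseline-negative patients per arm, Fisher's test at 5% rejects in about 13% of trials in the 20% vs 5% row (45 and 53 patients analysed). With no exclusion it rejects in 3.3% (56 per arm).

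**4. Possible bias with a true effect.** Take 50% (conventional) vs 20% (anterior), with assumed detection of 80% and 50% among heavy bleeders.

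- 15% conventional and 5% anterior excluded: (0.50 − 0.12) / 0.85 = 0.447 and (0.20 − 0.025) / 0.95 = 0.184. Difference 26.3 points, power 78.9%.
- 5% and 15% excluded: (0.50 − 0.04) / 0.95 = 0.484 and (0.20 − 0.075) / 0.85 = 0.147. Difference 33.7 points.

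**5. The statements side by side.**

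| | Exclusion criteria | Sample size section | Analysis |
|---|---|---|---|
| Threshold | 2000 cc or more | above 2000 cc | none given |
| Scope | blood tumour-cell analysis only | not limited | intention to treat |
| R1 | out of follow-up, data recorded | excluded, not limited | not mentioned |

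The threshold difference affects only a patient recorded at exactly 2000 cc. The scope and R1 differences matter more: an analyst cannot tell whether an R1 patient belongs in the primary comparison.

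**The case against.** The strongest reply is that the size of the problem rests wholly on assumptions. The documents give neither the share of patients reaching 2000 cc, nor its split by arm, nor their detection rate. With small or equal shares, or no link between bleeding and detection, the effect is negligible or zero. That stands, and it is why the tables include those cases.

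The exclusion may also have a sound laboratory motive: heavy loss may dilute the sample. The article gives no reason, though the full protocol may, and its absence here is not held against the plan. Dilution would reverse the direction of bias. It would not restore the protection of randomisation, and a sensitivity analysis serves the same purpose.

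A reader might go further and infer that heavy bleeders are the most manipulated patients and so shed the most cells. The documents do not say so. The Background links shedding to the extent of resection and manipulation, not to blood loss. A reader might also push the illustration in step 4 to a 39-point difference by assuming 80% detection among heavy bleeders in both arms, with 5% vs 15% excluded. In the anterior arm 0.15 × 0.80 = 0.12 of the 0.20 positives, or 60% of them, would then come from 15% of the patients. That figure should not be relied on.

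Finally, requiring a post-resection sample is itself a post-randomisation condition. This is true. It is much weaker than selecting on a compared outcome, and missing samples should be counted by arm.

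**Conclusion.** The concern holds as a defect in how the primary analysis set is defined. The blood-loss rule selects on a post-randomisation outcome, contradicts the intention-to-treat statement, and appears in two incompatible forms, one of which brings in R1 status, also known only after randomisation. These points follow from the text and need no assumed rates.

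The consequence is less certain. A reader might infer that the comparison is biased, or that it favours one technique. The documents support neither: bias is possible, not shown, and its direction and size cannot be fixed from them. With no true effect (35% in both arms) the assumed scenarios give:

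- zero, if exclusion is equal with the same detection among the excluded, or if detection is unrelated to bleeding;
- about 1 point at 5% vs 2% excluded;
- 3 to 6 points at 15% vs 5%, with 60–80% detection among the excluded;
- up to about 9 points at 20% vs 5% with 80%;
- the opposite sign if dilution lowers detection.

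With a true 50% vs 20%, a 15% vs 5% split in either direction gives about 26 to 34 points. The planned 150 contains no allowance for these exclusions.

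**What to change.** 1. Define the primary set as all randomised baseline-negative patients with a post-resection sample, analysed in the assigned arm, regardless of blood loss or margin status.
2. Remove the blood-loss exclusion from the primary analysis in both the exclusion criteria and the sample size section.
3. State in the sample size section that R1 status does not remove a patient from the tumour-cell analysis. The R1 follow-up rule concerns the survival endpoints and is a separate matter.
4. Keep the 2000 cc exclusion, with one threshold, as a named sensitivity analysis.
5. Report, by arm, the number reaching the threshold and the number without a post-resection sample.
6. Reconcile Exclusion criteria, Sample size, Clinical evaluation and Analysis. Removing patients whose technique was changed conflicts with analysis in the assigned arm. This concerns the analysis set only, not the surgeon's freedom to change technique.

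This should be settled before the interim analysis, because the stopping rule uses the same endpoint. Current status reports 61 randomised, and the interim is due after 75.

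The cost is an amendment to the wording and one extra analysis. The blood samples are already part of the protocol, and the planned 112 evaluable patients are preserved as far as these exclusions are concerned. The downside is that a few possibly diluted samples enter the primary analysis.
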